### Cost-effectiveness analysis

The cost-effectiveness analysis will take a societal perspective. The primary outcome will be quality adjusted life years (QALY) measured by the EQ-5D [43], a standardised instrument for measuring health outcomes (collected at baseline and follow-up), which is widely used in general population research internationally. The EQ-5D will be administered at multiple time points and the area under the line of their curve will estimated [48]. We expect that, at least in the short term, there will be little or no demonstrated effect on QALY. For this reason, the primary clinical outcome, reduction in alcohol consumption, will be a secondary outcome in the cost-effectiveness analysis.

Detailed information on resources associated with the provision of the intervention (training of clinical staff, screening and assessment, diagnostic and genetic tests, and medication) will be obtained from each clinical site’s electronic clinical records. The use of other health-care resources will be collected through data linkage of emergency department and inpatient hospital records and by self-report using a modified health services utilisation data collection form. Hospital utilisation will be costed with appropriate unit cost weights. Other health-care resources (general practice visits, etc.) will be costed using unit costs obtained from a range of sources including State Wage Awards [49], the Pharmaceutical Benefits Schedule [50] and the Manual of Resource Items published by the Pharmaceutical Benefits Advisory Committee [50]. Lost productivity and personal costs will be collected by structured self-report (HPQ: Clinical Trials Version) [44]. The HPQ contains questions about absenteeism (hours and days missed from work), and the quality and quantity of work while at the job (often referred to as presenteeism). All costs, including any related to adverse events, will be summed and combined with the outcome measure, and the incremental cost-effectiveness ratio:$$ \mathrm{ICER}=\left(\mathrm{Cost}\ \mathrm{of}\ \mathrm{topiramate}-\mathrm{Cost}\ \mathrm{of}\ \mathrm{naltrexone}\right)\times N\Big)/\left(\mathrm{Eff}\ \mathrm{topiramate}-\mathrm{Eff}\ \mathrm{naltrexone}\right). $$

Bootstrapping will be conducted to obtain reliable confidence intervals from skewed data, and cost-effectiveness acceptability curves calculated. Our analysis will account for any differences in sample groups if necessary.

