The majority of naltrexone pharmacogenetic studies have examined the role of rs1799971 (or Asn40Asp), a SNP in the gene encoding the mu-opioid receptor (*OPRM1*), as a moderator of treatment response. Most retrospective analyses have shown greater treatment efficacy in heavy drinkers with Asp40 who were treated with naltrexone [19, 20]. However, more recently, data from two prospective studies that oversampled the variant allele failed to show a moderating effect [21, 22]. These inconsistencies are most likely due to the sampling bias inherent in post hoc analyses of clinical trial data [21]. Prospective genotype-stratified trials are required to confirm retrospective observations from a secondary analysis of pharmacotherapy trials.

Accordingly, the current study aims to examine the treatment and cost-effectiveness of topiramate versus naltrexone in improving outcomes in active drinkers and prospectively to examine the moderating role of the rs2832407 polymorphism in *GRIK1* on treatment response. We hypothesise that:i.Topiramate-treated patients will significantly reduce their drinking, as measured by the number of HDDs, compared to oral naltrexone.ii.Topiramate treatment will be more cost-effective than oral naltrexone.iii.rs2832407 will have a moderating effect on drinking outcomes in topiramate-treated patients.iv.Comorbid clinical conditions (e.g. obesity, smoking rates and anxiety) will be significantly improved in topiramate-treated patients compared to those on naltrexone.

We will also conduct exploratory analyses of the moderating role of (i) the Asn40Asp SNP in *OPRM1* on drinking outcomes in naltrexone-treated patients and (ii) baseline clinical characteristics on treatment response to topiramate versus naltrexone. This article presents the protocol for the RCT and is written to comply with the recommended SPIRIT guidelines for RCT protocols (Additional file 1) [23].

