### Sample size calculations

Power is considered for a two-sided test at α = 0.05 and a within-subject correlation of 0.35–0.40 for repeated measures. For the primary aim, the naltrexone versus topiramate analysis (grouped by time), we considered power for the comparison of the topiramate and naltrexone groups to have a small-to-moderate effect size, Cohen’s *d* = 0.33, at week 7 that will persist through week 12 based on Baltieri et al. [12]. Therefore, we have more than 80% power to detect a small effect size with our recruiting aim of *N* = 180 (*N* = 90 in each group). For the secondary aim, analysis of the moderating effect of *GRIK1*, we consider just the topiramate-treated patients in Kranzler et al. [17] in which the CC versus A carrier groups were separated at week 6 by a moderate effect size. Therefore, we have more than 80% power to detect a moderate effect size with *N* = 90 (as per above). The frequency of the rs2832407 C allele in individuals of European descent is approximately 60–65%, with 41–43% C allele homozygotes [15]. Our sample size calculations, thus, account for a prevalence of approximately 42% of the responsive CC genotype. The moderating effect of *OPRM1* is an exploratory aim given that: (i) there have been several investigations of the moderating role of this SNP on naltrexone in alcohol patients and (ii) the prevalence of Asp40 carriers is 15–25% and potential under-sampling will, thus, reduce the power to test the effect.

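### The printed ICER multiplies only the cost difference by an undefined N; with costs and effects on the same basis, the ratio is inflated N-fold

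*Protocol article*

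**What the plan says.** Cost-effectiveness is the second hypothesis in the Background: "Topiramate treatment will be more cost-effective than oral naltrexone". The Cost-effectiveness analysis section names the main effect measure: "The primary outcome will be quality adjusted life years (QALY) measured by the EQ-5D". It describes the derivation as follows: "The EQ-5D will be administered at multiple time points and the area under the line of their curve will estimated". Reduction in alcohol consumption is the secondary effect measure; the Primary outcome section expresses consumption as heavy drinking days (HDDs) per week.

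On costs, the section says that all of them, adverse-event costs included, "will be summed and combined with the outcome measure, and the incremental cost-effectiveness ratio", and the formula follows. In the article's mark-up its numerator reads "Cost}\ \mathrm{of}\ \mathrm{topiramate}-\mathrm{Cost}\ \mathrm{of}\ \mathrm{naltrexone}\right)\times N", and the expression continues "N\Big)/\left(\mathrm{Eff}\ \mathrm{topiramate}-\mathrm{Eff}\ \mathrm{naltrexone". In plain notation, with ΔC for the cost difference and ΔE for the effect difference (topiramate minus naltrexone), this is ΔC × N) / ΔE.

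N is not defined there. The Sample size calculations section uses the letter for two quantities: "our recruiting aim of *N* = 180 (*N* = 90 in each group". The section also plans bootstrap confidence intervals and acceptability curves, and says in general terms that differences between the groups will be allowed for if needed.

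**The concern.** An incremental cost-effectiveness ratio divides a difference in cost by a difference in effect, both on the same basis. If both are means per participant, no sample size belongs in it. If both are arm totals with equal arms, the arm size cancels. A multiplier on the numerator alone therefore stays in the answer.

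This is a formula stated wrongly, not a detail left to a fuller document. It is the only expression the article gives for the quantity behind the second hypothesis. A ratio computed from it on a common basis could not be read as a cost per QALY or per HDD avoided. Any interval or curve built directly on that ratio would carry the same scaling.

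**Working it through.** The article gives no cost difference, effect difference or numerical ICER, so there is no figure to reproduce. The check is algebraic, with assumed inputs as illustration.

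**Inputs**
- Formula: ΔC × N / ΔE (Cost-effectiveness analysis section).
- N: 90 or 180 (Sample size calculations section).
- Arm size n = 90 (same section).
- Assumed, per participant: ΔC = 500 and ΔE = 0.02 QALY. The inflation factor does not depend on these values.

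**Reference value**

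ΔC / ΔE = 500 / 0.02 = 25,000 per QALY.

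**Brackets**

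The expression has two opening and three closing brackets. The surplus one stands directly after N and before the division sign. Restoring a partner at the start gives ((ΔC) × N) / (ΔE), so N still scales costs alone.

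**Four readings of the two terms**

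Arm totals are ΔC = 500 × 90 = 45,000 and ΔE = 0.02 × 90 = 1.8.

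| Cost | Effect | N = 90 | N = 180 | Multiple of 25,000 |
|---|---|---|---|---|
| mean | mean | 500 × 90 / 0.02 = 2,250,000 | 500 × 180 / 0.02 = 4,500,000 | 90 or 180 |
| total | total | 45,000 × 90 / 1.8 = 2,250,000 | 45,000 × 180 / 1.8 = 4,500,000 | 90 or 180 |
| mean | total | 500 × 90 / 1.8 = 25,000 | 500 × 180 / 1.8 = 50,000 | 1 or 2 |
| total | mean | 45,000 × 90 / 0.02 = 202,500,000 | 45,000 × 180 / 0.02 = 405,000,000 | 8,100 or 16,200 |

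The factor is exactly N in the first two rows. Only the third row, with N equal to the arm size, gives the right ratio.

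**Which reading is natural**

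The notation for cost and effect is symmetric. An area under a person's EQ-5D curve and a weekly HDD count are both quantities measured on one participant. That points to the first row, although the text does not say so.

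**How safe the third row is**

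It needs two arms of exactly N. Allocation is by minimisation, and the Statistical analysis section uses participants who took at least one dose, so equal analysed arms are not assured. Illustration with assumed figures: mean QALYs of 0.35 (topiramate) and 0.34 (naltrexone), with 88 and 92 analysed. The totals are 88 × 0.35 = 30.80 and 92 × 0.34 = 31.28. The difference in totals is −0.48, although the difference in means is +0.01. On this reading a modest imbalance can reverse the sign of the effect.

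**The case against.** The strongest reply is that the article never says whether cost and effect are means or totals, so the size of the error is not fixed. That stands: the multiple runs from 1 to 16,200 across the readings, and the N-fold figure is conditional on a common basis. The statement that costs are summed does not settle it either. It follows a list of cost categories and can mean adding categories within a patient rather than adding patients.

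The unmatched bracket suggests a typesetting slip, so the printed string may not be the calculation the analysts intend. That also stands as a limit, but it does not remove N from the numerator.

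A reader might go further and infer that the trial's ICER will be wrong by two orders of magnitude against any per-QALY threshold, and that the cost-effectiveness conclusion falls with it. The document does not support this. It states no threshold. A positive N cannot change the sign of either difference, so a finding that one drug is both cheaper and more effective would survive. Acceptability curves are planned as well, and the article does not say whether they would be built from the printed ratio or from the separate cost and effect differences.

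The general promise to allow for group differences is relevant to unequal arms, but it is too vague to repair the formula.

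**Conclusion.** The formula is misprinted or misstated and needs correcting. With cost and effect both as per-participant means, or both as totals over equal arms, it overstates the size of the ratio by a factor of N: 90 if N is the arm size, 180 if it is the total. This rests on the common-basis reading, which is natural but not stated. The one reading that rescues the formula is not stated either, and it depends on equal arms of exactly N.

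This is a should-fix point. Randomisation, sample size, data collection and the primary HDD analysis do not depend on it. The document does not show that the economic analysis would be run literally as printed.

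**What to change.** Delete the multiplier N, balance the brackets, and state:

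ICER = (mean cost per participant on topiramate − mean cost per participant on naltrexone) / (mean effect per participant on topiramate − mean effect per participant on naltrexone).

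Add that both differences are taken over the same participants and the same time horizon, and that the same definition serves QALYs and the alcohol-consumption outcome. The bootstrap and the acceptability curves should use these same per-participant differences.

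The cost is one corrected line in the protocol and, if the formula is repeated there, in the analysis plan. It needs no extra data and no change to the conduct of the trial.

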## Discussion

The TOP study will examine the therapeutic and cost-effectiveness of topiramate versus naltrexone in improving alcohol outcomes in active drinkers and will prospectively examine the moderating role of the rs2832407 polymorphism in *GRIK1* on treatment response. The trial will also examine the effectiveness of topiramate versus naltrexone on a range of comorbid conditions associated with AUD, including obesity, tobacco use and anxiety symptoms. It is critical for genetic association research to be both replicated and to be conducted prospectively to reduce the likelihood that observed associations were not due to type 1 errors. Similarly, prospective reporting of this clinical trial protocol contributes to clinical trial quality [51]. This report has been prepared in accordance with the SPIRIT protocol for reporting of clinical trial protocols [23].

The results of the TOP study will add to the current literature, insofar as it will be the first double-blind randomised comparison of naltrexone and topiramate and will also include a prospective design of a genetic moderator of the topiramate response. The secondary outcomes evaluated in this trial will provide clinically important information about patient groups that are likely to benefit from TOP treatment. The use of an objective laboratory marker of alcohol use is not novel and has been recommended for all alcohol treatment trials [52], but this will be the first topiramate trial to utilise phosphatidylethanol for this purpose. The use of SMS reporting is also an important measure to improve the quality of outcome measurement. Despite it being a self-report measure, SMS reporting occurs very close to real time. It reduces bias and can be used to validate self-reports made at study visits [53]. It is also the first cost-effectiveness analysis of topiramate in the treatment of AUD and the first comparative cost-effectiveness study of topiramate versus naltrexone.

Improving the therapeutic benefit of pharmacotherapy for AUD remains a challenge. The individualised selection of medication based on a patient’s genotype and clinical comorbidities is a potentially cost-saving strategy, as it may avoid the use of futile treatments in individuals unlikely to benefit from them. The TOP trial, thus, has the potential to facilitate the development of a personalised medicine approach and therefore, improve treatment for AUD.

### Trial status

The trial is now in the recruitment phase (commenced 20 June 2017).
